### Health economic analysis

A decision tree will be used to assess the cost-effectiveness of the CDR [48]. The prevalence of heart failure in patients presenting to primary care will be determined both from the study cohort and from a review of the epidemiological literature. The probability that patients with and without heart failure will be referred for echocardiography will be determined based on the test characteristics of both the CDR and of existing practice. The decision tree may be further refined depending on the power of the available data from the study; for example, distinguishing between patients with HF of different levels of severity (such as LVSD and HFpEF patients).

Cost and quality of life implications for patients at different branches of the decision tree will be extrapolated based both on data collected during the study and from the literature. Prospectively collected data on quality of life, clinical events and health care resource use will be used to estimate outcomes associated with using the CDR, NT-proBNP, their combination, or continuing with current practice. Since the study does not capture the full details of every acute event in the cohort, the cost and quality of life implications of such events will be imputed from the literature and standard UK sources of health economic information [49,50].

Outcomes associated with current practice will be estimated by using GP reported clinical judgment to predict their intentions for patients in the absence of using the CDR. In addition, the model will allow exploration of the effect on cost effectiveness of hypothetical scenarios involving altering the threshold peptide value for referral to echocardiography. Decreasing the threshold will cause more people to be referred for echocardiography, hence increasing costs but also improving outcomes. By using a suitable threshold cost per QALY cut-off (such as the threshold of £20,000 - £30,000 used by the National Institute of Health and Clinical Excellence) [51], the optimal threshold peptide value for referral can be estimated [52].

Costs will be evaluated from a health care provider perspective, with a lifetime time horizon. The effect of uncertainty in parameter values will be quantified by both univariate and probabilistic sensitivity analysis, and will be summarised using appropriate methods (cost-effectiveness plots and/or cost-effectiveness acceptability curves) [48].

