## Abstract

**Background:**

Heart failure is a major cause of mortality and morbidity. As mortality rates are high, it is important that patients seen by general practitioners with symptoms suggestive of heart failure are identified quickly and treated appropriately. Identifying patients with heart failure or deciding which patients need further tests is a challenge. All patients with suspected heart failure should be diagnosed using objective tests such as echocardiography, but it is expensive, often delayed, and limited by the significant skill shortage of trained echocardiographers. Alternative approaches for diagnosing heart failure are currently limited. Clinical decision tools that combine clinical signs, symptoms or patient characteristics are designed to be used to support clinical decision-making and validated according to strict methodological procedures. The REFER Study aims to determine the accuracy and cost-effectiveness of our previously derived novel, simple clinical decision rule, a natriuretic peptide assay, or their combination, in the triage for referral for echocardiography of symptomatic adult patients who present in general practice with symptoms suggestive of heart failure.

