## Background

Heart failure (HF) is a life-threatening, costly condition [1]. It affects at least 2.3% of adults over 45, rising to 4% in over 75 year olds [2]. HF markedly reduces quality and length of life [3], and treatment costs are high, second only to stroke and mainly due to high admission rates [4]; estimated to consume almost 2% (£751 million) of total NHS expenditure [5]. HF is a diagnostic challenge, as symptoms are non-specific and physical signs can be subtle [6-9]. Because outcomes in HF are linked to stage of disease and evidence-based treatments alter natural history as well as improve symptoms and prognosis [10-12], accurate early diagnosis and treatment is essential to reduce morbidity and mortality. As most patients with suspected HF are seen initially by GPs [6,13], the need for early and accurate diagnosis in primary care is essential to ensure optimum management and appropriate treatment is initiated rapidly.

Specialist review of symptoms and signs plus objective investigations, including echocardiography (Echo), is the established ‘gold standard’ for diagnosing left ventricular systolic dysfunction (LVSD) and increasingly suspected HF with a preserved ejection fraction (HFpEF) [14]. Diagnosing HF requires objective estimation of cardiac function (i.e. Echo) since determining the aetiology and stage of HF leads to different management choices such as initiation of angiotensin-converting enzyme (ACE) inhibitors [10], ß-blockers [11] and aldosterone antagonists in most patients with LVSD [15], cardiac resynchronization therapy for those with LVSD and broad QRS complex [1], or surgery where significant valve disease exists. These therapies improve symptoms, prognosis and quality of life, and can reduce healthcare utilisation and NHS costs. However, a difficulty is that performing Echo on all suspected HF patients would be costly as many patients are found not to have HF.

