Our systematic review [40] identified one unpublished study which had developed a decision tool based on simple clinical features [42]. In our individual patient data analysis [40,41] we further developed this tool and validated it on other primary care data sets. We found that a simplified model, based upon simple clinical features (Male gender, history of myocardial Infarction, basal Crepitations, oEdema: ‘MICE’) and BNP derived from one data set, was found to have good validity when applied to other data sets, with the area under the curve between 0.84 and 0.96, and reasonable calibration. A model substituting ECG for BNP was less predictive. Our systematic review concluded that BNP could substitute for ECG for determining referral to Echo and some patients could be referred with no prior tests on the basis of clinical features alone.

We shall establish the clinical utility of B-type NP tests in informing the diagnosis of diastolic HF as well as LVSD and valve disease. Additionally, we shall determine the probability thresholds of the CDR above which Echo would be the most cost-effective diagnostic strategy, taking into account patient quality of life and survival. The results will contribute to scientific progress by solving the problem wherein GPs have clinical uncertainty about whether an Echo should be done or not for a patient whom they suspect may have HF. There is now an opportunity to provide these data and to potentially demonstrate that the CDR can improve patient management concerning diagnostic accuracy, clinical decision-making and cost-effectiveness.

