### Primary and secondary endpoints

Primary outcomes include:

• Test performance of the CDR, estimating the sensitivity and specificity, positive predictive value and negative predictive value of the CDR for diagnosis of HF in symptomatic patients presenting with shortness of breath, lethargy, or ankle oedema of over 48 hours duration

• Test performance of the diagnostic accuracy of NT-proBNP for diagnosis of HF in symptomatic patients, including sensitivity, specificity, positive predictive value and negative predictive value

• Proportion of patients with LVSD or not (ejection fraction <40%) and HF or not

Secondary outcomes include:

• Combination of the CDR and NT-proBNP

• Modelling of CDR test performance and epidemiological data to ascertain the most cost effective strategy in the diagnosis of HF in primary care, incorporating data on quality of life (EQ-5D and SF12 questionnaires), clinical events and health care resource use

• Reliability of GP clinical judgment alone in diagnosing HF

• Reliability of individual clinical features

• Reliability of ECG interpretation

• Estimation of the best performing cut-offs for NT-proBNP to maximise diagnostic yield and for maximizing cost-effective referrals

• Determine the use of variable echocardiographic markers of diastolic function in the diagnosis of HF with preserved ejection fraction

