Selection bias is a key issue in diagnostic accuracy studies. This bias would occur if GPs enrolled only those patients they believed to have a high probability of heart failure. This would mean more symptomatic or more severe cases would dominate the study sample and result in an over-estimation of the test-accuracy of the CDR [57,58]. In our study, the consecutive inclusion of all symptomatic patients will minimise the risk of introducing this type of bias. GPs will be asked to refer all patients over 55 years of age presenting with the target symptoms regardless of whether or not heart failure is suspected by the doctor and excluding patients with pre-existing confirmed heart failure. Verification bias is also a potential limitation and may occur if patients with low pre-test probability of heart failure were to be excluded from undergoing reference standard diagnostic testing to verify the diagnosis of heart failure. This would result in an over-estimation of test sensitivity [58]. Performing all diagnostic assessments on all patients included in the study will minimise this potential source of bias.

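### The economic comparison names four strategies and omits echocardiography for everyone without triage, so it can rank those four but cannot identify the most cost-effective strategy

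*Protocol article*

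**What the plan says.** The Health economic analysis section describes a decision tree. Prospectively collected data will be used to "estimate outcomes associated with using the CDR, NT-proBNP, their combination, or continuing with current practice". The probability of referral in patients with and without heart failure "will be determined based on the test characteristics of both the CDR and of existing practice". Scenarios, described as hypothetical, will move the peptide threshold, and an optimal value will be sought at £20,000 to £30,000 per QALY. No range for the threshold is given.

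The aims are wider than this list. Under Primary and secondary endpoints, the modelling is meant "to ascertain the most cost effective strategy in the diagnosis of HF in primary care". The Background says the study will "determine the probability thresholds of the CDR above which Echo would be the most cost-effective diagnostic strategy".

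On echocardiography without triage, the article says two things. The abstract holds that "All patients with suspected heart failure should be diagnosed using objective tests such as echocardiography". The Background sets the option aside because "performing Echo on all suspected HF patients would be costly as many patients are found not to have HF", and gives no figure. It is nowhere named as a modelled strategy.

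**The concern.** A strategy is the most cost-effective only relative to the alternatives in the comparison. Referring everyone is the upper limit of every triage rule: no case is missed at triage, the number of echocardiograms is at its maximum, and no triage assay is needed. Whether the extra echocardiograms are worth their cost is the question a cost-per-QALY model exists to answer, and the Background answers it by assertion.

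If the branch is missing, the CDR could come out best of four while referral of everyone has the higher net benefit at the plan's own threshold. The Discussion says the modelling will indicate whether further research is unnecessary, should the strategy dominate. That conclusion would also rest on an incomplete set.

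**Working it through.** **Inputs from the Sample size section:** prevalence 30%, CDR sensitivity 94%, CDR specificity 48%, N = 500. These are planning values from the earlier individual patient data analysis, not results of this study.

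**The plan's own figure.** N = 500 gives 150 patients with heart failure and 350 without. The normal-approximation half-widths are:
- sensitivity: 1.96 × √(0.94 × 0.06 / 150) = 3.8 points (stated: within 4)
- specificity: 1.96 × √(0.48 × 0.52 / 350) = 5.2 points (stated: within 6)

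The stated precision is reproduced. The exact 95% interval for 141/150 is 88.9% to 97.2%.

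**CDR against referral of everyone, per 1,000 patients:**
- with heart failure and referred by the CDR: 300 × 0.94 = 282; not referred: 18
- without heart failure and referred by the CDR: 700 × 0.52 = 364
- total referred by the CDR: 282 + 364 = 646; not referred: 354
- extra echocardiograms per extra case reached: 354 / 18 = 19.7

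**Sensitivity of that ratio:**

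| Change | Calculation | Ratio |
|---|---|---|
| Sensitivity 88.9% | 369.3 / 33.3 | 11.1 |
| Sensitivity 97.2% | 344.4 / 8.4 | 41.0 |
| Prevalence 20% (per 500) | 198 / 6 | 33.0 |
| Prevalence 40% (per 500) | 156 / 12 | 13.0 |

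**Break-even, with assumed unit costs.** The article gives none. Cost per extra case = 19.7 × cost of one echocardiogram, before any assay saving. Dividing by £20,000 or £30,000 gives the QALY gain per extra case at which referral of everyone would be preferred to the CDR.

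| Assumed cost | Cost per extra case | Break-even at £20,000 | Break-even at £30,000 |
|---|---|---|---|
| £50 | £983 | 0.05 | 0.03 |
| £100 | £1,967 | 0.10 | 0.07 |
| £200 | £3,933 | 0.20 | 0.13 |
| £400 | £7,867 | 0.39 | 0.26 |

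**A second set of assumptions, per QALY.** Take £70 to £250 per echocardiogram, £0 to £25 per assay, half of patients referred directly, and 0.1 to 0.5 QALY per case:
- low end: (354 × 70 − 500 × 25) / 18 / 0.5 = £1,364
- high end: (354 × 250) / 18 / 0.1 = £49,167

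The range lies on both sides of £20,000 to £30,000.

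**What the peptide scenarios leave out.** With the threshold lowered until everyone is referred, patients without a direct-referral feature are still charged the assay. Under the same assumptions, at £70 per echocardiogram and £25 per assay, the cost per extra case relative to the CDR is:
- refer-all limit of the CDR, assay still charged: (354 × 70) / 18 = £1,377
- refer-all with no assay: (354 × 70 − 500 × 25) / 18 = £682

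At £250 per echocardiogram the two figures are £4,917 and £4,222. The limit of the scenario is always the costlier version, by an amount that depends on the assay price and on the share of patients referred directly.

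**The case against.** **The list may not be closed.** The sentence describes how study data will be used, the tree may be refined, and a journal article condenses the full plan. This has some force. But the only refinement given as an example is by severity of heart failure, the referral probabilities are tied to the CDR and existing practice, and no part of the article names referral of everyone as an option.

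**The threshold work nearly contains the missing strategy.** A very low optimal probability threshold would mean referring almost everyone, and so would a peptide threshold near zero. If that limit won with the assay charged, the no-assay version would win all the more. This narrows the gap to cases where the assay cost decides the ranking. It does not close it, because the article does not say that the scenarios extend that far or that a no-assay version will be costed.

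**Capacity.** The article sets universal echocardiography aside for more than price: it also cites a shortage of trained staff, delay and variable access. That is a fair constraint on implementation. It is a reason to state the constraint alongside the comparison, not to omit the comparison.

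**The money figures are assumed.** This stands in full. They leave out downstream treatment and event costs, although the model has a lifetime horizon. They also treat a patient not referred as never diagnosed, whereas the Background describes repeat consultations and later diagnosis.

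**Two stronger readings.** A reader might infer that the model can say nothing useful about the CDR. The article does not support that: objective 4 asks only for the cost-effectiveness of using the CDR, and the comparison with current practice serves it. A reader might also infer that echocardiography for all would be preferred. Nothing in the article shows this, because it gives neither unit costs nor QALY gains.

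**Conclusion.** The point holds in a limited form. The named strategies do not match the stated aim of finding the most cost-effective one, and the question of the probability above which echocardiography is most cost-effective cannot be answered fully without the refer-all end of the scale. The size that rests on the plan's own figures is 19.7 extra echocardiograms per extra case reached (11 to 41 over the exact limits for sensitivity, with specificity held at 48%). This takes referral of everyone as 100% sensitive as a referral rule. The costs per QALY rest wholly on assumed values and show only that the strategy cannot be excluded beforehand. Conclusions about the CDR against current practice, and the ranking of the four strategies among themselves, are unaffected.

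**What to change.** In the Health economic analysis section:

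1. Add a fifth model branch in which every eligible patient is referred for echocardiography with no triage assay (referral sensitivity 100%, specificity 0%).
2. Rank all strategies in one fully incremental, net-benefit analysis at £20,000 to £30,000 per QALY.
3. State limited echocardiography capacity as a constraint on how the ranking is read.

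If the branch is not added, the claim should be restricted to the most cost-effective of the four strategies compared.

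The cost is one extra branch. No new data are needed, since the Potential risks and burdens section says every participant has the full diagnostic assessment. The CDR may look less favourable. The change adds a comparator to the model and proposes no clinical rule.

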### Ethical considerations

The study has full approval from South Birmingham Research Ethics Committee, reference number 09/H1207/121. We shall ensure that participation in the study does not lead to inferior medical care by performing the diagnostic assessments within seven days of GP referral and by informing the patient’s GP of the clinical assessment results and any clinical abnormalities uncovered within seven days. Therefore, study patients will receive a higher standard of care than would be likely in routine practice. Post-study medical care will be provided by patients’ GPs.

### Participant consent

We shall ensure that patients are fully informed about all aspects of the study prior to obtaining informed consent. Study duration, assessments and the voluntary nature of participating will be discussed before obtaining written informed consent. We shall record all requests to withdraw from the study.

### Potential risks and burdens

There should be no risk to patients since a full diagnostic assessment, including the reference standard diagnosis, which is non-invasive, is carried out on all patients in the study and in a timely manner. Therefore, patients are receiving a higher standard of care than would be likely in routine practice.

### Data quality assurance

The data manager will oversee all data collection with built in validation and regular reports to ensure the integrity of data. The database will be monitored exclusively by the data manager and the statistician. Data will be extracted from the database and imported into statistical software packages, SAS and STATA. The statistician will then perform further validation checks through exploratory data analysis, identifying any blank fields, outliers and logical inconsistencies between fields. Any problems detected will be then verified and corrected by the data manager. The project manager will ensure that the conduct of the study complies with the currently approved protocol, with Good Clinical Practice, and all applicable R&D regulatory procedures. All study activities will be performed in accordance with the University of Birmingham Standard Operating Procedures.

### Research governance

The study will be conducted in accordance with the Guidelines for Good Clinical Practice, the Research Governance Framework for Health and Social Care, 2005 and the Data Protection Act 1998. Patient involvement has ensured that both the patient information and consent forms are relevant to the patients the study attempts to improve services for. All relevant regulatory approvals have been sought prior to commencing the study and the study registered with the UK Clinical Research Network (UKCRN No: 7944). We have obtained ISRCTN registration (ISRCTN17635379) prior to patient enrolment.

The study will be conducted in compliance with Data Protection legislation, with particular attention given to the emphasis on privacy and on processing of personal data extending to disposal or destruction and disclosure to a third party. Participants shall be informed that information may be accessed during the study by Regulatory Authorities or the relevant NHS Trust in compliance with the Data Protection legislation. Data processing and linkage of personal information will be subject to the strictest ethical safeguards of anonymity, with documents assigned a numerical code. All data shall be held securely and treated with the strictest confidentiality.

### Indemnity and sponsorship

The University of Oxford has arrangements in place to provide for negligent and non-negligent harm arising from participation in the study for which the University is the Research Sponsor. NHS indemnity operates in respect of the clinical treatment which is provided.

## Discussion

The REFER Study is a multicentre, Phase II study designed to prospectively validate a CDR to improve the diagnosis of heart failure in primary care. HF is a diagnostic dilemma for the general practitioner [6,8,13,53]. In the absence of an accurate method of identifying patients with HF, triage of patients for echocardiography in primary care is variable. As a result HF diagnosis is often delayed, misdiagnosed, or treated incorrectly [53]. The main characteristic of the REFER study is that it examines a symptomatic adult population presenting in general practice.

A major problem with all the studies we uncovered in our review of the diagnostic test systematic reviews is spectrum and referral bias since most were based on observational screening studies rather than symptomatic presenting patients, and some were hospital rather than community based [40]. Only a prospective study design with consecutively recruited symptomatic patients can avoid or minimise these potential biases. Another major strength of the REFER study is that the study has been designed according to strict methodological standards to determine the diagnostic accuracy of the CDR [35,43,54-56]. Moreover, the study’s design will provide data on the impact of the availability of the NT-proBNP result on the reference standard diagnosis of heart failure. These data are of clinical significance, given that the current NICE algorithm for heart failure diagnosis envisages NT-proBNP being used principally as a triage test to determine which patients should have echocardiography [16]. However, in diagnosis of heart failure with preserved ejection fraction, it may be that a raised natriuretic peptide level is of diagnostic value in its own right. Further, the results will provide data on optimum natriuretic peptide cut-offs which, as far as we are aware, are not yet available. Additionally, the planned modelling will indicate whether further research is not necessary if the strategy dominates or the technology fails. An intermediate result would enable accurate powering for any future Phase III trial.

